#### Health insurance claims data

This study will only focus on the health-care costs of patients, which will be measured using the health insurance claims data of the participants, which are available at Vektis. Vektis is a national information centre for all the health insurance companies in the Netherlands. The centre collects all data on the health-care utilization and health-care costs of all Dutch residents [26]. Health insurance claims data will be used to examine whether the health-care costs of an intervention patient (PC+) is different to the health-care costs of a control patient. To compare the health-care costs of an intervention patient with that of a control patient, the health insurance claims of each patient participating in the intervention or control group will be used, with a focus on GP care, PC+ and hospital care. Moreover, it has been decided to take into account the health-care costs per participant over a period of 6 months. The starting point is the date of referral to the PC+ centre (intervention group) or the hospital-based outpatient cardiology care (control group).

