The practice-based study focuses on a cardiology Primary Care Plus (PC+) centre. In this pioneer site PC+ implies substitution of specialist care in the hospital setting with specialist care in the primary care setting and it is designed for patients with non-acute and low-complexity related health complaints. Since virtually all specialists are hospital-based in the Netherlands, PC+ is a new form of health care. In the cardiology PC+ centre cardiologists provide consultations in the primary care setting. During the PC+ consultation the patients receive a comprehensive screening and afterwards the cardiologist sends his recommendations for further treatment (if needed) to the GP. For example, the specialist informs the GP about whether a referral to hospital care is needed. Based on the recommendation, the GP discusses the options for further treatment with the patient. Moreover, within PC+ the GP remains clinically in charge of the patient. PC+ strengthens the gatekeeping and coordinating role of the GP by intensifying the collaboration and communication between the specialists and the GPs. The PC+ intervention aims to improve the health of the population and patients’ experience of care and to reduce the number of referrals to hospital care (as well as hospital-based outpatient specialist care) in order to reduce health-care costs growth. In this study, the PC+ intervention is compared to care-as-usual, both are described in detail in the methods section. This paper describes the design of the evaluation of the cardiology PC+ intervention, combining qualitative and quantitative methods.

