Finally, it is supposed that the introduction of PC+ will lead to reduced health-care costs by: 1) fewer referrals to hospital-based outpatient care because of the introduction of PC+, 2) lower costs in PC+ than in hospital-based outpatient care, due to lower overhead costs (i.e. the same cardiology screening will costs less in PC+), 3) less use of additional hospital-based services because it is supposed that a significant number of the patients referred to PC+ will not be referred to hospital care afterwards, but will remain in the primary care setting, and 4) GPs will gain more knowledge because of the enhanced collaboration and communication with the cardiologists. Hence, in the long term, it is possible that they will refer fewer patients, to either PC+ or hospital-outpatient care, for a cardiology screening and instead treat the patients themselves.

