#### Health-care costs

Health-care costs will be measured using health insurance claims data. This study will not cover all related health-care costs but will only focus on health-care costs (including patients’ compulsory deductible). Out-of-pocket payments and indirect costs made from a societal perspective (e.g. labour market, informal care) will not be included. The health-care costs per participant is measured over a period of 6 months after the consultation at the PC+ centre or the hospital-based outpatient cardiology care. This concerns data regarding health-care costs on primary care, PC+, hospital care and diagnostics.

Efficiency of care means, according to the IOM, avoiding waste, particularly waste of equipment, supplies, ideas and energy [19]. With regard to this research, it will be measured whether the number of consultations of patients, hospital admissions and referrals will decrease after the implementation of PC+, which is related to efficient use of equipment and health-care professionals and time of patients. Efficiency of care will be measured using data from the cardiology PC+ centre, the hospital and Vektis. The data will consist of the following items: 1) the average number of consultations at the hospital of a patient over a period of 6 months; 2) the average number of hospital admissions of a patient over a period of 6 months; and 3) the number and percentage of patients that are referred to hospital care after PC+.

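### Costs are compared per referred participant and only hospital referrals are counted, so the plan cannot tell substitution from added volume and cannot by itself support a claim of lower overall costs

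*Protocol article*

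**What the plan says.** **The aim.** In the Background, PC+ is meant "to reduce the number of referrals to hospital care (as well as hospital-based outpatient specialist care) in order to reduce health-care costs growth". In Objectives and underlying premises of PC+, "it is supposed that the introduction of PC+ will lead to reduced health-care costs by" four routes. These are fewer hospital referrals, a lower unit cost in PC+, less use of additional hospital services, and GPs learning from cardiologists, so that in the long term "it is possible that they will refer fewer patients, to either PC+ or hospital-outpatient care".

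**The cost outcome.** Under Health insurance claims data, "it has been decided to take into account the health-care costs per participant over a period of 6 months", and "the health insurance claims of each patient participating in the intervention or control group will be used". The contrast is stated there too: "Health insurance claims data will be used to examine whether the health-care costs of an intervention patient (PC+) is different to the health-care costs of" someone in the control group. The Health-care costs section under Outcome parameters uses the same unit: "The health-care costs per participant is measured over a period of 6 months after the consultation".

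**The volume outcomes.** Table 1 lists a number of referrals. The Experience of care section defines it as referrals to hospital-based outpatient cardiology care, examined for a fall between 2013 and 2017. The efficiency items are average hospital consultations per patient, average hospital admissions per patient, and the number and percentage of PC+ patients sent on to hospital.

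**Entry to PC+.** All GPs in the region may refer. Study population says that there are no specific referral criteria at present and that less severe patients should go to PC+. The Objectives section expects shorter waiting times.

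**The concern.** Spending on this group is the number of patients seen multiplied by the cost of each. The claims analysis sees only the cost per patient, among people already referred by one route or the other. The referral count sees part of the volume, namely the hospital part. The number of patients entering PC+ is in no outcome.

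A patient moved from hospital to PC+ and a patient whom the GP would otherwise have managed alone look the same in the PC+ group. The first replaces a hospital cost and the second adds one. With open entry, a shorter wait and a preference for milder cases, the second kind is possible.

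Both planned results could then be favourable while overall spending is unchanged or higher. The Discussion says that the results will lead to recommendations which the site can use in extending PC+ to four more specialities, so a per-patient saving read as an overall saving would matter.

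**Working it through.** **Inputs from Sample size and power calculation.** There were 1755 eligible hospital outpatient referrals in 2013, out of 14,978 cardiology referrals. The relevant difference is a 50% fall, to 878.

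**The protocol's own figures.** 1755/14,978 = 11.7%, stated as 12%. 1755 × 0.5 = 877.5, stated as 878, which leaves 1755 − 878 = 877 referrals to move. The sample size follows from (1.96 + 0.84)² × 0.09 × 0.91 × 2 / 0.06² = 356.7, or 357, close to the stated 358 per group. That calculation concerns referral proportions. The protocol gives no effect size for costs.

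**Assumptions, since the protocol gives no cost ratio.** A hospital patient costs 1. A substituted patient costs c in PC+. An extra patient, who would not have been referred before, costs k. Hospital referrals reach 878 exactly. Moved patients would have cost the same in hospital as those who stayed. No GP cost is avoided for extra patients.

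**Formulas.** With E extra patients:

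- Total cost relative to 2013 = (878 + 877c + E·k) / 1755
- Break-even: E = 877(1 − c) / k

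| c | Saving with E = 0, in hospital-patient units | Break-even E if k = c | Break-even E if k = 0.5 |
|---|---|---|---|
| 0.9 | 87.7 | 97 (5.6% of 1755) | 175 (10%) |
| 0.8 | 175.4 | 219 (12.5%) | 351 (20%) |
| 0.7 | 263.1 | 376 (21.4%) | 526 (30%) |
| 0.6 | 350.8 | 585 (33.3%) | 702 (40%) |

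**Worked line.** For c = 0.8, the saving is 877 × 0.2 = 175.4. Dividing by k = 0.8 gives 219, and dividing by k = 0.5 gives 351.

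**Results that point in opposite directions.** With c = k = 0.8 and 1250 PC+ patients, total cost is (878 + 1250 × 0.8)/1755 = 1878/1755 = 107% of the 2013 level. The per-participant comparison shows a 20% saving, and the hospital target is met.

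**Case-mix dilution.** With c = 0.8 and 400 extra patients at k = 0.5, the unadjusted PC+ mean is (877 × 0.8 + 400 × 0.5)/1277 = 0.706 instead of 0.80. Total cost is (878 + 701.6 + 200)/1755 = 101.4%. This mean is not the planned estimate, which is propensity-adjusted.

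**GP costs.** If an extra patient would otherwise have incurred a GP cost g that is now avoided, k is replaced by k − g and every break-even volume rises.

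**The case against.** **Volume is not ignored.** A reader might infer that the plan measures only cost per patient. It does not: the hospital referral count from 2013 to 2017 is a planned outcome, and the sample size is built on hospital referrals. This stands, and it narrows the point. Hospital volume is tracked and combined volume is not.

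**The study limits itself.** Health insurance claims data says that the study looks only at patients' health-care costs. The unit-cost and additional-services premises are per-patient mechanisms, which the planned contrast addresses, and the premise about GPs learning is hedged as a long-term possibility. This is fair as far as it goes. The Objectives section still ties the introduction of PC+ to reduced costs, and the per-participant contrast cannot carry that conclusion.

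**Induced demand is conjecture.** A reader might infer that PC+ will draw in extra patients. No section reports or predicts it, and the Background says that the GP payment system does not encourage referral to specialist care. This stands. The absence of referral criteria makes added volume possible and does not show that it occurs.

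**Adjustment.** A reader might infer that every extra mild patient makes PC+ look cheaper. Data analysis plans a propensity score whose example variables include baseline health-care costs, age and GP characteristics. This would reduce dilution for what is measured. It cannot deal with unmeasured severity, and no adjustment among participants can recover how many patients entered.

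**Size.** Charging extra patients the full PC+ cost while calling them mild is inconsistent, so the table also shows a lower cost for them. At c = 0.8 this moves break-even from 219 to 351.

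**Conclusion.** The point holds as a mismatch between the aim and the outcomes. The aim is lower health-care costs through the introduction of PC+, whereas the outcomes are cost per referred participant and hospital referrals. A lower per-patient cost together with a halving of hospital referrals is compatible with higher total spending, and nothing planned would show which has happened.

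The size depends on assumed costs. With hospital referrals at 878, PC+ at 0.8 of the hospital cost and no GP offset, the saving disappears at 219 to 351 extra patients (12.5% to 20% of 1755) as the cost of an extra patient goes from 0.8 down to 0.5. Across the ratios tabulated, the range is 97 to 702.

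The documents do not support the stronger conclusion that PC+ raises spending or that the cost comparison is invalid. As an estimate of cost per referred patient, subject to confounding, it answers a legitimate question.

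**What to change.** 1. Keep the per-participant comparison and word its conclusion as cost per referred patient, not as reduced health-care costs overall.
2. Extend the planned 2013–2017 referral analysis to report, for each year, PC+ referrals plus eligible hospital outpatient referrals, using one fixed definition of eligibility. The PC+ centre registers each patient with a referral date, and the hospital register already supplied the 2013 eligible count.
3. Show the break-even extra volume beside the cost result as a sensitivity figure, using the observed fall in hospital referrals and a range of costs for extra patients.
4. Claim a total-cost reduction only if combined volume has not risen beyond break-even.

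A direct comparison of total cost with 2013 is less clean. Claims are planned for participants only, so no 2013 cost is available, and less severe patients are directed to PC+, which may leave a more severe control group. The control mean should not serve as the 2013 cost unless that is stated.

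The cost is wording, repeated use of one eligibility rule on two registers, and a small table. The cost conclusion may become less favourable. The volume comparison remains before-after, so a rise could also reflect the ageing and chronic illness that the Background describes.

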### Outcome parameters

The outcome parameters are related to the Triple Aim principle and are focused on (1) population health, (2) experience of care and (3) health-care costs [6]. All outcome parameters of the quantitative study, including the dimension, outcome, concept, method and time of data collection, are summarized in Table 1. The outcome parameters, related measures and selected questionnaires are based upon suggested measures by the Institute of Healthcare Improvement to operationally define and measure the Triple Aim [27].

#### Population health

Population health will be measured with three generic validated questionnaires, namely the EQ-5D-5 L, the EQ-VAS and the Short Form Health Survey (SF-12).

The EQ-5D-5 L incorporates descriptions and valuations of health status and reflects how patients value their own health state. The questionnaire comprises the dimensions mobility, self-care, usual activities, pain/discomfort and anxiety/depression [28, 29]. The scores range from −0.33 to 1 (worst imaginable to best imaginable health state), using the Dutch utility tariff [30]. Instead of the EQ-5D-3 L 3-level version, we have chosen to use the EQ-5D-5 L 5-level, because this appears to be a valid extension of the 3-level. Several studies indicate that the measurement properties of the EQ-5D-5 L are superior to the EQ-5D-3 L in terms of feasibility, reliability, ceiling effects, discriminatory power and convergent validity [31–33].

The EQ-VAS (visual analogue scale) is added; this is a reflection of how patients value their own health state (range from 0 to 100).

The SF-12 is a subset of the larger SF-36 [34]. The questionnaire comprises eight health aspects, namely physical functioning, role limitations because of physical health problems, bodily pain, general health, vitality (energy/fatigue), social functioning, role limitations because of emotional problems, and mental health (psychological distress and psychological well-being) [34–37]. The reliability of the SF-12 is high (> 0.80) [34–37]. In addition, three items from the SF-36 are added to calculate the Mental Health Inventory score, comprising the dimensions feeling nervous, feeling downhearted and blue, and feeling happy [34].

#### Experience of care

The experience of care will be measured using the perspective of the patient, i.e. the patient’s interaction and experience with the health-care system. The outcome parameters are based upon the six dimensions of health-care performance of the IOM: safety, effectiveness, equity, timeliness, patient-centredness and efficiency [19]. As mentioned above, efficiency will be included in the dimension health-care costs.

Effectiveness of care will be measured with the EQ-5D-5 L questionnaire and the percentage of referrals to hospital-based outpatient cardiology care. On the one hand, effectiveness will be measured using the EQ-5D-5 L scores, where it is analysed whether the health of the population is improved after a follow-up of 3 months. On the other hand, effectiveness will be measured using the number of referrals to hospital-based outpatient cardiology care, where it is analysed whether this number is decreased in the period from 2013 to 2017.

Timeliness of care will be examined by measuring the waiting time (in days) between the day the patient is referred by his GP and the day of the first consultation with the cardiologist.

Patient-centred care will be measured using items based on the Consumer Quality (CQ) index. The CQ index is a standardized method for measuring experiences of patients with health care [38]. The questionnaire (T1) includes 30 questions about the experiences of the patients with health care, with specific regard to their experiences with the health-care professionals (e.g. *‘Did you feel welcome and at ease?’* and *‘Did the health-care professionals listen attentively?’*).

Safety of care will be measured using data that will be made available by the hospital concerning: 1) hospital admissions; 2) emergency care visits.

Equity of care will be examined by performing subgroup analysis on all outcome measures regarding educational level (high versus low) and age (lower than median and higher than median).

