### Sub-study 1: the quantitative study

#### Aim

The aim of the quantitative part is to measure the effects of the PC+ intervention on the population’s health, patients’ experience of care and health-care costs. To measure the effects the researchers will use the following sources: patient questionnaires, data from the cardiology PC+ centre, data from the regional hospital and health insurance claims data. The data will be collected at four different time points, namely at baseline, before the patient has the first consultation with the cardiologist (T0), a week after the first consultation (T1), 3 months after the first consultation (T2) and 6 months after the first consultation (T3). The outcome parameters, including the dimensions, outcomes, concepts, methods and time frame, are summarized in Table 1.

**Table 1 Tab1:** Overview of the outcome measurements

Dimension	Outcome measure	Concept	Method	Data collection time			
				T0	T1	T2	T3
Population’s health	Health status, health-related quality of life	EQ-5D-5 L	Questionnaires	X	X	X	
		EQ-VAS		X	X	X	
		SF-12		X		X	
Experience of care	Effectiveness	EQ-5D-5 L	Questionnaires	X	X	X	
		Number of referrals	Data^a^	X		X	X
	Timeliness	Time between referral of the GP and appointment at the PC+ centre/hospital	Questionnaires	X	X		
	Patient centred	Questions about the experiences of patients with health care	Questionnaires		X		
	Safety	% Hospital admissions	Data^a^				X
		% Emergency care visits					X
	Equity	Subgroup analysis, e.g. educational level and age	Questionnaires	X		X	
Health-care costs	Health-care costs: primary care, PC+, secondary care and diagnostics	Health insurance claims data	Data^a^				X
	Efficiency	Number of consultations	Data^a^				X
		% Hospital admissions					X
		% Patients referred to hospital after PC+					X

T0 – at baseline: before the consultation

T1 – within a week after the consultation

T2 – 3 months after the consultation (follow-up)

T3 – 6 months after the consultation (follow-up)

^a^Data of the PC+ centre, the hospital and Vektis

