### Sample size and power calculation

The sample size and power calculation is based on the referral data of the hospital in 2013 extracted from its registration system. The data of 2013 show that 12% (1755 referrals to hospital-based outpatient cardiology care) of all referrals (14,978 referrals) to the cardiology department of the hospital are eligible for PC+. These eligible patients are referred to hospital-based outpatient cardiology care, which provides, among other health care, the same health care as the PC+ centre. A decrease of 50% in the number of referrals to hospital-based outpatient cardiology care is seen as a relevant difference. So, the number of referrals eligible for PC+ will decrease from 1755 (12% of the total referrals to cardiology) referrals to 878 (6% of the total referrals to cardiology). While assuming a power of 80% and a significance level of 0.05, 358 patients per group (intervention as well as control) are required. Taking into account a dropout of 20%, a sample size of 429 patients per group is required, so this study needs to include 858 patients in total.

To calculate the sample size the following formula was used to compare proportions:$$ N=\frac{{\left({Z}_{\alpha }/2+{Z}_{\beta}\right)}^2\ast p\kern0.2em \left(1-p\right)\left(r+1\right)}{{\left({p}_{0-}\kern0.2em {p}_1\right)}^2\ast r} $$

With the following meaning of the abbreviations:

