**Table Taba:** 

Zα/2 = critical value of the normal distribution at α/2; α = 0.05	1.96
Zβ = critical value of the normal distribution at β; β is 0.2	0.84
p0 = expected proportion of referrals eligible for PC+ at baseline	0.12 (12%)
p1 = expected proportion of referrals eligible for PC+ 1 year after the intervention is implemented	0.06 (6%)
p = (p1+ p0)/2	0.090
r = ratio of patients per group	1

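### The referral outcome is an uncontrolled 2013-to-2017 comparison with several definitions, so a fall cannot by itself be credited to PC+ as less overuse

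*Protocol article*

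**What the plan says.** The protocol article describes the referral outcome in four places.

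- **Experience of care.** Effectiveness is measured partly by "the percentage of referrals to hospital-based outpatient cardiology care". Two sentences later the analysis is of the number of such referrals, "where it is analysed whether this number is decreased in the period from 2013 to 2017".
- **Sample size and power calculation.** The 2013 baseline is "12% (1755 referrals to hospital-based outpatient cardiology care) of all referrals (14,978 referrals", and "A decrease of 50% in the number of referrals to hospital-based outpatient cardiology care is seen as a relevant difference". The table of terms defines "p0 = expected proportion of referrals eligible for PC+ at baseline" (0.12) and "p1 = expected proportion of referrals eligible for PC+ 1 year after the intervention is implemented" (0.06).
- **Table 1.** The row "Number of referrals" is marked at T0, T2 and T3, which are time points relative to each patient's consultation.
- **Objectives and underlying premises of PC+.** Fewer hospital referrals are expected as a result of PC+. This is read as reduced overuse and listed as the first route to lower costs.

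The setting matters too. The region has one hospital (The pioneer site), and every GP in it takes part (The intervention).

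**The concern.** A before-after count in a single region supports attribution to an intervention only if something shows what would have happened without it. None is stated for this outcome, and the rest of the design does not supply one. With all GPs exposed, the region has no series from unexposed practices. The mixed model with a propensity score under Data analysis works on patients. A calendar-period count is not a patient outcome, and every control patient is a hospital referral by definition.

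Displacement is a second difficulty. A patient sent to PC+ drops out of the hospital first-referral count whether or not that patient needed a specialist. The count can halve while as many people as before, or more, see a cardiologist.

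At stake is the reading of the only outcome with a power calculation. A fall could be reported as less overuse when it shows drift, or a change of address for the same referrals. The differing definitions add to this, because number and share can move differently and neither can be recorded at a patient's T2 or T3.

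**Working it through.** **1. The plan's own figure.** Inputs from the table of terms: z values 1.96 and 0.84, p0 = 0.12, p1 = 0.06, p = 0.09, r = 1.

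N = (1.96 + 0.84)² × 0.09 × 0.91 × 2 / (0.12 − 0.06)² = 7.84 × 0.1638 / 0.0036 = 356.7, so 357 per group.

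The stated 358 is reproduced to within one patient. The two proportions are two calendar periods of one hospital's referrals (1,755/14,978 = 11.7%, and 878/14,978 = 5.9%). The result is nevertheless applied to the concurrent intervention and control groups.

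**2. The definitions side by side.**

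| Place | Scale | Time frame |
|---|---|---|
| Experience of care, first mention | percentage | not given |
| Experience of care, analysis sentence | number | 2013 to 2017 |
| Sample size and table of terms | share of all cardiology referrals | 2013, then 1 year after implementation |
| Table 1 | number | T0, T2, T3 per patient |

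**3. Drift, if the raw count were tested.** The article names no test for this count. I assume a two-count Poisson comparison, z = (1,755 − n)/√(1,755 + n), at two-sided 0.05.

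- n = 1,641: z = 114/√3,396 = 1.956, not significant.
- n = 1,640: z = 115/√3,395 = 1.974, significant. The smallest significant fall is thus 115, or 115/1,755 = 6.6%.

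The true background trend is not in the document, so the annual declines below are assumptions, each with no PC+ effect. The expected 2017 count is 1,755 × (1 − d)⁴. The chance of declaring a decrease is approximately Φ(z − 1.96).

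| Assumed annual decline d | Expected 2017 count | Fall | z | Chance of a declared decrease |
|---|---|---|---|---|
| 1% | 1,686 | 3.9% | 1.18 | 22% |
| 2% | 1,619 | 7.8% | 2.35 | 65% |
| 3% | 1,554 | 11.5% | 3.50 | 94% |

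To produce the full 50% fall, drift alone would have to run at 1 − 0.5^(1/4) = 15.9% a year.

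**4. Drift, if a share is used.** Dividing by all cardiology referrals removes a trend common to them all, but not one specific to low-complexity referrals. If only the eligible referrals fell by 2% a year and the other 14,978 − 1,755 = 13,223 stayed constant, the share would move from 11.7% to 1,619/(1,619 + 13,223) = 10.9%.

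**5. Displacement (assumed figures).**

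- GPs send half of the same 1,755 patients to PC+. Hospital first referrals become about 878, which meets the 50% target, and specialist screenings stay at 1,755. If 0% to 50% of those seen at PC+ are then sent on, between 878 and 1,316 patients still reach the hospital. The net fall is 50% to 25%.
- Hospital eligible referrals are 878 and PC+ receives 1,200. Eligible referrals total 2,078, and 2,078/1,755 = 1.18, a rise of 18%. Across all cardiology referrals the total is 14,978 − 877 + 1,200 = 15,301, a rise of 2.2%. With 1,000 at PC+ instead, the rises are 7.0% and 0.8%. With 877, both are zero.

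**The case against.** Several points on the other side stand.

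- **Substitution is the purpose.** PC+ is meant to move specialist consultations out of the hospital, so a fall in hospital first referrals is an intended result. Onward referral after PC+ is recorded under Health-care costs. This means that the count is a fair measure of substitution, but not that it shows less overuse. The onward referrals are a separate item, not combined with the count.
- **A denominator exists.** A reader might infer from the analysis sentence that only a raw count is available. The document does not support that. The same paragraph mentions a percentage, and the sample size section gives 1,755 of 14,978. The fault is that number and percentage are not reconciled.
- **The 65% is not the plan's error rate.** No Poisson test is named, and the stated relevant difference is 50%, which modest drift would not reach. The figure shows only how small a fall would pass a simple test of decrease.
- **Costs do not hang on this count.** They come from claims data, with a concurrent control group and propensity adjustment.
- **The horizons can coexist.** One year after implementation may be a planning assumption, and 2013 to 2017 an observation window.
- **Model detail may sit in a fuller document.** That is so, but the article itself fixes the reading as a decrease over the period and attributes it to PC+.

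**Conclusion.** The concern holds in this form. The analysis as stated is an uncontrolled before-after reading of an outcome whose scale and time frame differ between sections. A fall can come from drift in low-complexity referrals or from displacement, and so cannot alone support the premise of reduced overuse.

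The direction of the problem follows from the text; its size does not. The 6.6% threshold and the 65% at an assumed 2% annual decline depend on a Poisson test of the raw count and on a trend that the document does not report. The 18% rise in PC+-eligible referrals (2.2% in all cardiology referrals) depends on an assumed 1,200 PC+ referrals.

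A reader might go further and conclude that a 50% fall would be spurious, or that the cost results are compromised. The document supports neither. Drift alone would need about 15.9% a year to halve the count, and costs are measured separately against a concurrent group.

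**What to change.** - **One definition throughout:** PC+-eligible hospital referrals per calendar period, with all cardiology referrals as denominator. State whether PC+ referrals belong in that denominator. Delete the T0, T2 and T3 marks for this row of Table 1.
- **Report alongside it:** PC+ plus hospital referrals together, and hospital referrals including those sent on after PC+. These separate substitution from a change in total demand.
- **Comparison series:** the non-eligible cardiology referrals (13,223 in 2013). Where the registration yields a consistently classified series, fit an interrupted time series with a pre-PC+ trend.
- **Otherwise:** present the 2013-to-2017 change as descriptive, and withdraw its attribution to PC+.

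The cost is an additional extract from the hospital and PC+ registrations, with no added burden on patients. The harder part is classifying eligible referrals the same way across years. The article shows them for 2013 only, gives no PC+ opening date, and says under Study population that referral to PC+ has no specific criteria. A full segmented regression therefore cannot be taken for granted, but the single definition and the combined totals do not depend on it.
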